## Abstract

**Background:**

Reoperation rates in clavicular fractures and acromioclavicular (AC) joint dislocations are high, often indicated for plate removal due to plate prominence and poor cosmesis. The recently designed 2.7 mm variable angle locking compression plate (VA-LCP®) Clavicle Plate and 2.7 mm VA-LCP® Clavicle Hook Plate (J&J MedTech) are intended to have an improved plate-to-bone fit, are precontoured, and have a low profile. Additionally, the Clavicle Hook Plate has a more anatomically adapted hook design to reduce the risk of painful osteolysis leading to earlier plate removals. All screw holes in these plates accept 2.7 mm screws. Primary objectives of this observational, post-marketing, prospective, multicenter case series are to gather early and mid- to long-term evidence on the clinical performance, safety, and usability of the 2.7 mm VA-LCP Clavicle Plates and 2.7 mm VA-LCP Clavicle Hook Plates, specifically to describe (1) safety, (2) clinical performance, (3) functional outcomes, (4) patient-reported outcomes (PROs) and (5) usability and surgeons' experience with the devices.

**Methods:**

Approximately 76 patients with clavicle fractures and primary surgical treatment with the 2.7 mm VA-LCP Clavicle Plate or 2.7 mm VA-LCP Clavicle Hook Plate will be enrolled prospectively over 15 months. Outcome measures include adverse events related/potentially related to the investigational device, clinical performance, functional outcomes (QuickDASH), PROs (PROMIS® upper extremity score, local pain, discomfort, and plate prominence), and radiographic outcomes. Data will be collected at baseline, 2w, 6w, 3m, 6m, 1y and 2y after surgery. The surgeons' experience with and perceived utility of the devices will be surveyed. Interim analysis will be performed when 30 patients per group have reached 6 months after surgery. Long-term outcomes will be evaluated using 2-year follow-up results. A Statistical Analysis Plan will be prepared before final analysis summarizing the descriptive statistics to be used.

**Discussion:**

The study described in this protocol on patients with clavicular fracture or AC joint dislocations undergoing surgical fracture fixation aims to gather first evidence on the clinical performance, safety, and usability of the 2.7 mm VA-LCP Clavicle Plates and 2.7 mm VA-LCP Clavicle Hook Plate Systems. This study will provide valuable data from a standard-of-care setting and may help design future comparative studies for relevant performance parameters.

**Clinical Trial Registration:**

https://clinicaltrials.gov/study/NCT04921865?term=NCT04921865%20&rank=1, identifier NCT04921865.

## Introduction

1

There is still controversy and lack of consensus regarding not only surgical indications but also treatment of acute displaced clavicle shaft fractures and acute high-grade displaced acromioclavicular (AC) joint injuries (1–3). As surgical treatment has been increasingly used (1), higher complication and reoperation rates observed have led some to caution against overtreatment of displaced midshaft clavicular fractures (1, 4–6). After surgical treatment, reported reoperation rates in clavicular fractures range from 10%–84% (4–7) and up to 67% in AC joint dislocations (5). The need for plate removal is most often due to plate prominence and poor cosmesis due to the subcutaneous position of the clavicle and the bulky standard 3.5 mm implants. Galdi et al. examined whether using a lower profile 2.7 mm reconstruction plate would lead to better clinical outcomes and lower removal rates when compared with a 3.5 mm reconstruction plate in AO/OTA (Arbeitsgemeinschaft für Osteosynthesefragen/Orthopedic Trauma Association) type B clavicle fractures (8). The thinner 2.7 mm plates provided higher rates of cosmetic acceptability but did not demonstrate a statistically significant difference in reoperation rates for plate removal (8). Similarly, a recent retrospective comparative study also found that there was no statistically significant difference in rate of removal between 2.7 mm plates and 3.7 mm plates (9). Other studies have shown that clavicle fractures fixed with 3.5 mm reconstruction plates on the superior (subcutaneous) clavicle surface were more likely to exhibit plastic deformation, whereas constructs utilizing 2.7 mm reconstruction plates were more likely to fail by plate breakage (4).

The cost of clavicle fracture and AC dislocation treatment is high, ranging from a 2-year mean of US$27,635 [standard deviation (SD): US$68,173] to US$23,096 (SD: US$28,746), respectively (5), and up to GB£5000 for reoperations (7). Improving surgical methods and technologies could therefore reduce healthcare system costs through reduced unplanned reoperations and device removals. Additionally, predictable anatomic variance in clavicle morphology has been identified (10, 11), and understanding this variance could not only help improve the design and adaptation of clavicle implants, reducing the need for reoperations, but could also aid in implant selection (11).

The J&J MedTech 2.7 mm variable angle (VA) locking compression plate (VA-LCP®) Clavicle Plate System and the 2.7 mm VA-LCP® Clavicle Hook Plate System were designed to have an improved plate-to-bone fit. The plates have been pre-contoured taking into consideration the predictable anatomical variance of clavicle morphology and the correlation between individual patient height and clavicle length (11). The plates have a low profile to reduce construct prominence, soft tissue irritation, and related pain. All screw holes in these plates accept 2.7 mm screws, which is an important design adaptation in comparison to previous LCP 2.7/3.5 mm Clavicle Systems. Mechanical testing has shown that when the recommended screw configuration for each system is used, the 2.7 mm VA-LCP Clavicle Plates have higher construct static strength and equivalent construct fatigue strength compared with J&J MedTech 3.5 mm LCP Superior Clavicle plates (12).

The design rationale of the implant preferred pathway allows—for the first time—creation of a clavicle plate system matching the anatomy in a much higher number of cases. Further, the fixation strategy of the J&J MedTech 2.7 mm variable angle (VA) locking compression plate (VA-LCP®) Clavicle Plate System and the 2.7 mm VA-LCP® Clavicle Hook Plate System is new as the fracture-site centered-plate position is abandoned. Additionally, traditional clavicle hook plates, which were frequently used for the treatment of lateral clavicle fractures and acromioclavicular joint injuries, exhibit sub-optimal hook and plate geometry. Consequently, the hook is commonly directed towards the posterolateral corner of the acromion and does not match with the undersurface of the acromion (13), which might induce a raised point contact, osteolysis around the hook and/or subacromial impingement, and ultimately necessitate earlier implant removal. Both, the smaller plate design of the VA-LCP clavicle button hook plate, the anatomical plate design of the VA-LCP Clavicle Hook Plates and the anatomical hook design (10° anterior rotation; 16° inclination) are designed to address these issues. This new design will provide a better match of the hook to the undersurface of the acromion, and bring the tip of the hook more anterior, away from the posterolateral corner of the acromion.

This observational, post-marketing, investigator-initiated, prospective, multicenter case series aims to gather early and mid- to long-term evidence on the clinical performance, safety, and usability of the J&J MedTech 2.7 mm VA-LCP Clavicle Plate and 2.7 mm VA-LCP Clavicle Hook Plate Systems.

## Methods and analysis

2

### Study design and setting

2.1

This is an observational, post-marketing, prospective, multicenter case series on patients with clavicular fractures or dislocations of the AC joint undergoing surgical fracture fixation with either the 2.7 mm VA-LCP Clavicle Plate and 2.7 mm VA-LCP Clavicle Hook Plate Systems (J&J MedTech, Zuchwil, Switzerland). Table 1 summarizes study sites currently included. Currently, seven sites are participating in the study. Ethics approval has been obtained for six sites and is pending for one site. Thus far, 43 patients have been enrolled, of whom 42 meet the eligibility criteria.

**Table 1 T1:** Current participating sites.

Name	Country	Region
Klinik Ottakring, Vienna	Austria	Europe
Universitätsklinikum Freiburg, Freiburg	Germany	Europe
Universität Münster, Münster	Germany	Europe
Prisma Health Richland Hospital, Colombia	USA	North America
Atrium Health Wake Forest Baptist, North Carolina	USA	North America
Corewell Health, Grand Rapids, Michigan	USA	North America
Luzerner Kantonsspital, Lucerne	Switzerland	Europe

### Objectives

2.2

The objectives are to collect early and mid- to long-term evidence on the clinical performance, safety, and usability of the J&J MedTech 2.7 mm VA-LCP Clavicle Plate and 2.7 mm VA-LCP Clavicle Hook Plate System, specifically (1) safety, (2) clinical performance, (3) functional outcomes, (4) patient-reported outcomes (PROs), and (5) usability and surgeons' experience with the devices.

### Study procedures

2.3

All treatments will be performed per local standard of care (SoC). Baseline information, treatment details, and outcomes will be collected in a customized, searchable database (REDCap Cloud Electronic Data Capture system (https://www.redcapcloud.com/) (14, 15). Post-treatment care and follow-up visits will be conducted according to standard procedures at participating sites but will take place within predefined time windows; if the 12-month post-hook plate removal visit is not foreseen at the participating site, the visit can take place remotely. Radiographic images will only be taken if part of the local SoC.

#### Inclusion criteria

2.3.1

▪Patients aged ≥18 years▪Unilateral clavicle injuries are considered for inclusion in the study. The patient must be undergoing primary surgical treatment within 21 days of injury using either of the following devices according to the manufacturer's instructions for use:
○2.7 mm VA-LCP® Clavicle Plates are used for fixation of clavicle bone fragments. Hereinafter referred to as Clavicle Plates○2.7 mm VA-LCP® Clavicle Hook Plates are used for fixation of lateral clavicle fractures and dislocations of the acromioclavicular joint. Hereinafter referred to as Clavicle Hook Plates▪Expected ability to attend postoperative follow up (FU) visits▪Ability to provide informed consent

#### Exclusion criteria

2.3.2

▪Contraindications to the Clavicle Plates
○Stable clavicle fractures, i.e., fracture which is not indicated for internal fixation○Fixation of sternoclavicular joint○Systemic infection or infection localized to the site of the proposed implantation▪Contraindications for the Clavicle Hook Plates
○Stable lateral clavicle fractures, i.e., fracture which is not indicated for internal fixation○Fixation of sternoclavicular joint○Systemic infection or infection localized to the site of the proposed implantation▪Concomitant nerve or vessel injury▪Polytrauma (Injury Severity Score ≥16)▪Body mass index ≥40 kg/m^2^▪Uncontrolled severe systemic disease or terminal illness▪Intraoperative decision to use other implants is taken

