#### Recruitment

2.3.3

The recruitment period will be 15 months, during which at least 76 patients are planned to be enrolled. The participating sites will identify all eligible patients according to the defined inclusion and exclusion criteria. Eligibility assessment will be performed by the investigator and/or adequately trained research team member(s). The eligibility assessment includes but is not limited to an inquiry about the interest and willingness of the patient to participate in the study. Eligible patients identified after treatment (e.g., in case of an acute trauma followed by an emergency surgery) can be consented and enrolled at the latest by the time of discharge. Data collection for the study in the case report form (CRF) is not allowed without the documented agreement of the patient.

All consented patients included in the study will be allocated a unique patient number. Each site will keep an identification list linking the patient number to personal information. The identification list is always kept in a safe and locked place. Sites are not allowed to share the identification list with any third party except for the sponsor representative, legal authorities, and EC/IRB who may access the identification list during on-site monitoring/auditing performed on site.

All consented patients should be followed up within the study for a maximum of 2 years, except if their study participation is prematurely terminated.

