##### Surgeons' evaluation

2.3.7.4

Surgeons will be asked to evaluate their subjective experience with the Clavicle Plate/Clavicle Hook Plate system using the following two 5-point Likert scale questions:
Surgical time (skin-to-skin) required for fracture reduction and fixation (answers ranging from “much less time than with other implants” to “much more time than with other implants”)Surgeons' impression of the device fit (answers ranging from “implant fitted well, no contouring required” to “implant required contouring medially and laterally”).

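### Patients switched to another implant during surgery are excluded, so fit, surgeons' evaluation and intraoperative deficiency results describe mainly cases in which the study plate was implanted

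*Protocol article*

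**What the plan says.** All references are to the protocol article.

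- **Exclusion criteria (2.3.2).** The last criterion is "Intraoperative decision to use other implants is taken". It covers any change of implant during the operation, whatever the cause.
- **Inclusion criteria (2.3.1).** Inclusion is tied to the device: "The patient must be undergoing primary surgical treatment within 21 days of injury using either of the following devices".
- **Recruitment (2.3.3).** Eligible patients first identified after the operation "can be consented and enrolled at the latest by the time of discharge". Data entry in the case report form "is not allowed without the documented agreement of the patient".
- **Objectives (2.2).** The fifth objective is "usability and surgeons' experience with the devices".
- **Surgeons' evaluation (2.3.7.4).** One of two five-point items is the surgeon's "impression of the device fit". Section 2.4.2 plans counts and percentages per category for it.
- **Tables 2 and 3; Device deficiencies (2.3.7.8).** Deficiencies are recorded from the intraoperative visit onward, and all are to be reviewed.
- **Termination of participation (2.3.6).** The reasons for termination include treatment not being started under the study and ineligibility found after enrolment. The reason goes on a dropout form. Use of the data collected is permitted but not required.

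**The concern.** The other exclusions describe the patient, the injury or the indication. This one describes something that happens in theatre and that may be caused by the device under study. A surgeon who tries the study plate, finds that it does not fit or is defective, and changes to another implant has met the least favourable usability result. That is the case the criterion takes out of the study.

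This matters because fit is central to the rationale. The Introduction presents the plates as designed for better fit to bone and says that the system matches the anatomy in many more cases than before. That is a statement about a proportion, and a proportion needs the attempts that did not end in implantation. The Discussion wants the results to inform later comparative studies, so a favourably selected usability estimate would carry forward.

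**Working it through.** **Step 1. Follow a converted patient through each consent route.**

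| Route | What the protocol does | What remains on record |
|---|---|---|
| Identified after surgery, consent possible up to discharge | Only eligible patients may be enrolled; a converted patient is already ineligible | Nothing in the case report form |
| Consented before surgery (Visit 1 in Tables 2 and 3) | Leaves under the termination rules | Reason on the dropout form; use of data optional |

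On the first route the loss occurs at data capture. An analysis-population definition in the SAP cannot recover a record that was never made. On the second route the reason is captured, but no section shown makes conversion an outcome.

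**Step 2. Check whether the fit item could register a conversion.** Its stated range is "answers ranging from “implant fitted well, no contouring required” to “implant required contouring medially and laterally". Both ends describe a plate that was used, with or without contouring. Neither describes a plate that was set aside. Conversion therefore needs its own measure and cannot simply be added to the denominator of this scale.

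**Step 3. Reproduce the protocol's sample size.** Section 2.4.1 asks for 30 evaluable patients per group with 20% dropout: 30 / (1 − 0.20) = 37.5, rounded up to 38 per group, and 2 × 38 = 76. This matches the protocol and is not in dispute.

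**Step 4. Show what a conversion proportion would look like.** The document gives no conversion rate *c*, so a range is assumed. With 38 implanted patients in a group, the number of attempts is N = 38 / (1 − c), rounded, and the number of conversions is k = N − 38. The interval is the 95% Clopper-Pearson interval that section 2.4.2 already uses for risks.

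| Assumed c | Attempts N | Conversions k | k/N | 95% interval |
|---|---|---|---|---|
| 0% | 38 | 0 | 0% | 0 to 9.3% |
| 2% | 39 | 1 | 2.6% | 0.1 to 13.5% |
| 5% | 40 | 2 | 5.0% | 0.6 to 16.9% |
| 10% | 42 | 4 | 9.5% | 2.7 to 22.6% |
| 15% | 45 | 7 | 15.6% | 6.5 to 29.5% |

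If both groups are pooled (76 implanted), 5% gives 4/80 = 5.0% (1.4 to 12.3%) and 15% gives 13/89 = 14.6% (8.0 to 23.7%).

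In every row, results restricted to implanted patients would look the same. In groups of this size, two conversions move the upper limit from 9.3% to 16.9%.

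**Step 5. Look for an anchor in the document.** Section 2.1 reports 43 enrolled, of whom 42 are eligible: 1/43 = 2.3%. The reason for that one patient's ineligibility is not given, and patients converted and never enrolled would not appear in this count. It therefore neither supports nor excludes any row of the table.

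**The case against.** The strongest reply is that this is a descriptive case series with no hypothesis, that inclusion is defined by the device used, and that describing implanted cases is a legitimate aim. That stands. It is why converted patients can stay out of the follow-up outcomes.

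A reader might infer two stronger points that the protocol does not support:

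- **That results come only from cases where the device worked.** Implanted cases can still show contouring medially and laterally, deficiencies, adverse events, reoperation and removal, and all of these are collected. The selection is on implantation, not on good performance.
- **That conversions enter no analysis at all.** Patients consented before surgery have their reason recorded, and their data may be used. The deficiency section is not limited to completed implantations. Analysis populations are left to the SAP, which is not shown. The patient-flow figure, adapted from STROBE and also not shown, may list exclusions with reasons.

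Three further points are fair. A change of implant may have nothing to do with the device. Enrolment after surgery is an allowance, with emergency surgery as its example, and the protocol does not say how often it will be used. The size of the effect is entirely assumed.

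What the reply does not answer is the route that leaves no record, the absence of conversion as a planned usability outcome in the text shown, and the silence of the limitations paragraph in the Discussion, which lists many other sources of bias.

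**Conclusion.** The point holds in a limited form. Eligibility depends on an intraoperative event that may be caused by the device. As a result, the fit, surgeons' evaluation and intraoperative deficiency results describe only, or mainly, cases in which the study plate was implanted. For the usability objective the direction may favour the device.

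The size cannot be computed from the protocol. The table above (0 to 15.6% per group) rests on assumed conversion rates of 0 to 15% and on 38 implanted patients per group. It does not estimate what will happen, and it does not separate device-related from other conversions.

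It would also go too far to recompute the fit percentages with abandoned cases counted as poor fit. The scale's stated range does not cover a plate that was not implanted, and some conversions will have other causes. The follow-up outcomes and the target of 76 are not affected. This is a worthwhile, cheap improvement to the usability reporting, not a defect that undermines the study.

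**What to change.** Keep converted patients out of the follow-up outcomes, and make these changes:

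1. Log every case in which the study plate was attempted and then changed, with the reason: fit, device deficiency or other. Use the existing dropout form for consented patients, and an anonymous site count for those never consented.
2. Report conversions divided by attempted cases, with a Clopper-Pearson interval and split by reason, as a separate usability outcome.
3. Include deficiencies that led to conversion in the device-deficiency table.
4. Label the fit percentages as conditional on implantation, leaving their denominator as it is.
5. Add the selection to the stated limitations.

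The cost is one extra field and one extra table. Enrolment was still under way at the time of the article (43 patients), so prospective capture remains possible for the rest. The main weakness is that the count may be incomplete for patients who never consented, since no case report form data may be held for them; the report should say so.

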#### Recruitment

2.3.3

The recruitment period will be 15 months, during which at least 76 patients are planned to be enrolled. The participating sites will identify all eligible patients according to the defined inclusion and exclusion criteria. Eligibility assessment will be performed by the investigator and/or adequately trained research team member(s). The eligibility assessment includes but is not limited to an inquiry about the interest and willingness of the patient to participate in the study. Eligible patients identified after treatment (e.g., in case of an acute trauma followed by an emergency surgery) can be consented and enrolled at the latest by the time of discharge. Data collection for the study in the case report form (CRF) is not allowed without the documented agreement of the patient.

All consented patients included in the study will be allocated a unique patient number. Each site will keep an identification list linking the patient number to personal information. The identification list is always kept in a safe and locked place. Sites are not allowed to share the identification list with any third party except for the sponsor representative, legal authorities, and EC/IRB who may access the identification list during on-site monitoring/auditing performed on site.

All consented patients should be followed up within the study for a maximum of 2 years, except if their study participation is prematurely terminated.

#### Data collection

2.3.4

Tables 2, 3 show data to be recorded for Clavicle Plates and Clavicle Hook Plates. Figure 1 presents the planned patient flow.

**Table 2 T2:** Study schedule for patients with clavicle plates (lateral, shaft, and medial).

Assessment parameters	Pre- intra- and postoperative visits*							
	Visit 1	Visit 2	Visit 3	Visit 4	Visit 5	Visit 6	Visit 7^#^	Visit 8^#^
	Screening/preoperative	Intraoperative (Day 0)	2 (±1) weeks	6 (±1) weeks	3 months (±2 weeks)	6 (±1) months	12 (±1) months	24 (±2) months
Patient information/consent^1^	X							
Eligibility^1^	X							
Patient characteristics	X							
Surgical details		X						
Adverse events		X	X	X	X	X	X	X
Device deficiencies		X	X	X	X	X	X	X
Bone healing				X	X	X	X	X
Surgeons’ evaluation		X						
QuickDASH	X^2^		X	X	X	X	X	X
Patient-reported outcomes^3^								
PROMIS Upper Extremity	X^2^		X	X	X	X	X	X
Local pain			X	X	X	X	X	X
Local discomfort			X	X	X	X	X	X
Plate prominence			X	X	X	X	X	X
Implant removal^π^			X	X	X	X	X	X
Images (x-ray/CT scan)^4^	X	X	X	X	X	X	X	X

CT, computed tomography.

* All postoperative follow-up visits with the defined time windows are calculated from the day of surgical treatment (i.e., Day 0).

